## Abstract

**Background:**

Pregnancies at high risk for adverse health outcomes for mother and offspring often require long-term antenatal hospitalization and/or frequent outpatient visits. We have developed a telemonitoring home care service for high-risk pregnancies that has been integrated into the Electronic Patient Journal System of our department. We will compare clinical safety, patient-reported outcome measures, and use of healthcare resources compared to standard practice for hospital admissions and/or outpatient visits.

**Method:**

The home monitoring of high-risk pregnancies study is an ongoing observational study. Eligible women with a pregnancy requiring intensified obstetric follow-up (e.g., preterm premature rupture of membranes, hypertensive disorders of pregnancy, or a previous adverse obstetric outcome) are offered study inclusion to either standard care at the hospital or the home telemonitoring group, depending on available home monitoring equipment. Pregnant women included for home monitoring will be telemonitored according to relevant clinical practice for inpatients, including the use of cardiotocography, blood pressure monitoring, C-reactive protein, and temperature measurement, and they will provide self-registration of relevant clinical symptoms. A telecare patient communication system will prompt rapid contact with the hospital in the case of unfavorable registered clinical parameters or subjective symptoms. The home telemonitored women will attend hospital visits for fetal ultrasound assessment at individually assigned intervals. Patients undergoing in-hospital care will serve as the control group in this study and receive standard care. The primary outcome is a composite of severe maternal and perinatal adverse outcomes (sepsis, eclampsia, cerebral hemorrhage, acute respiratory distress syndrome, liver rupture, pulmonary embolism, amniotic fluid embolism, hemolysis, elevated liver enzymes, low platelets, HELLP without hemolysis, and disseminated intravascular coagulation), including fetal or neonatal mortality, maternal mortality, and signs of severe organ damage. Secondary outcomes include other adverse maternal and fetal/neonatal health outcomes, patient-reported outcomes, and economic cost analyses.

**Discussion:**

The implementation of a home care service for women with high-risk pregnancies requiring intensified surveillance is expected to be equally safe and more comfortable and convenient for the women, with lower economic costs.

**Clinical Trial Registration:**

Clinicaltrial.gov, NCT05763069.

## Introduction

The surveillance of mother and fetus is crucial for detecting early warning signs of maternal and/or fetal distress in pregnancies with an increased risk for adverse maternal and/or fetal outcomes (1, 2). If worrying maternal and/or fetal signs during pregnancy are not recognized and treated appropriately, the risk of mortality and morbidity is increased for both (3, 4). The lack of appropriate treatment may potentially have lifelong health consequences for the mothers and infants who survive. Surveillance in high-risk pregnancies aims to optimize early diagnosis, treatment, and timing for delivery in order to optimize health outcomes (3, 4). Specialized obstetric surveillance, including cardiotocography (CTG; registration of the fetal heart rate pattern and uterine contractions), blood pressure, and urine and blood analyses, often requires antenatal hospitalization and/or frequent outpatient visits until delivery.

High-risk pregnancies that often require intensified surveillance include those with hypertension during the pregnancy (e.g., chronic hypertension, gestational hypertension, and preeclampsia) and those with preterm premature rupture of membranes [pPROM; preterm premature (prior to 37 weeks of pregnancy) rupture of fetal membranes prior to onset of labor], the latter conferring a risk of preterm birth and/or chorioamnionitis, with increased risk of maternal and/or fetal death. In addition, some women with a history of adverse obstetric outcomes have a propensity for recurrence (e.g., previous intrauterine fetal demise, fetal growth restriction, or severe preeclampsia), thereby requiring intensified surveillance in the following pregnancy to optimize maternal and offspring health outcomes.

Recent technological development has generated new opportunities for health surveillance outside the hospital, i.e., at home. Home monitoring systems for high-risk pregnancies, with the opportunity for patient registration of CTG, have not been tested or established in most countries, including Norway. After the planning of the home monitoring of high-risk pregnancies (HOME) study, two articles reporting on outcomes after home monitoring of high-risk pregnancies have been published: one retrospective study of 8 years of practice in Denmark (5) and one randomized controlled trial from the Netherlands (6). Both concluded that home monitoring may be a safe alternative to inpatient hospital care for selected women with high-risk pregnancies. Home monitoring of blood pressure in pregnancy poses challenges, as blood pressure can rise rapidly during pregnancy. Monitoring of blood pressure at home in pregnant women with gestational hypertension has, however, demonstrated better compliance with guidelines, likely lowering the burden on public health resources (7).

Any change in clinical practice needs to be thoroughly evaluated, including an evaluation of clinical outcomes. Thus, in this study, clinical safety, patient-reported outcomes, and healthcare economics following the introduction of home monitoring in high-risk pregnancies will be investigated. Ultimately, personalized follow-up with more telemonitoring opportunities and flexibility may enable the much in-demand specialist resources at obstetric departments (e.g., midwives and obstetricians) to focus on the patients with the greatest need for in-hospital follow-up.

The hypothesis in this clinical study is that home monitoring in selected high-risk pregnancies does not increase the risk of severe adverse maternal or fetal outcomes for women and their fetuses compared to similar pregnancies being followed up through hospitalizations and/or frequent outpatient visits. We also anticipate increased patient-reported satisfaction in line with positive patient expectations from general technology-enabled care solutions (8) and findings from our own preclinical expectation study related to the HOME study (9). Finally, we expect that the freeing up of hospital beds will reduce hospital costs and thereby result in a positive health economic assessment, despite the increased device costs and reorganization of the hospital’s follow-up system.

## Materials and methods

### Study setting

The observational HOME study has been carried out in southeastern Norway, primarily at Oslo University Hospital (OUH) in Norway's capital, Oslo, which has the largest Obstetric Department in Norway, with 8,000 deliveries annually. Another hospital in the region, Drammen Hospital, with 2,000 deliveries annually, will also recruit some patients to the study.

Norway offers pregnant women free-of-charge antenatal, delivery, and postpartum care. Women deemed at high risk for adverse pregnancy outcomes, either due to current pregnancy complications or previous adverse obstetric outcomes, are offered intensified follow-up according to a national expert guideline (3).

The observational study protocol for this study was posted on ClinicalTrials.gov in 2023 (10 March 2023: ref: NCT05763069). The first woman was recruited to the hospital-monitored group in December 2022. The first woman monitored at home was recruited in June 2024, following a 2-year period of study adaptation due to General Data Protection Regulation (GDPR) issues and technology solution developments for the transfer of home-registered data to the hospital's electronic patient journal systems.

### User involvement

The HOME study has involved user groups in the planning of the study, including the local hospital advisory user group and the Norwegian SIDS and Stillbirth Society. The latter society also provides advisory help during all trial phases, as a member of the steering group and as a non-academic named collaborator in the HOME study grant obtained from the Research Council of Norway (ref. 326650).

Prior to recruiting women to the HOME study, a qualitative study was conducted to address user perspectives on home-based telemonitoring as an alternative to hospital admissions and/or frequent outpatient visits. Hospitalized women with ongoing high-risk pregnancies, women with a history of stillbirth in a previous pregnancy, midwives, and obstetricians (total *n* = 21) were interviewed (9). The results showed that the participants not only acknowledged the benefits and potential of home monitoring but also highlighted their concerns regarding clinical safety and responsibility. Home monitoring of high-risk pregnancy was problematized in terms of personal/individual factors, such as the need for personalized training, eligibility assessments of individuals, and empowerment to undertake and cope with a more active patient role. A sense of shared responsibility was regarded as crucial to maintain safety, particularly when acute or critical situations emerge (9).

In line with these user expectations, published in 2022, we developed user instruction protocols for home monitoring training while the patient is still in the hospital. We developed clinical questionnaires regarding patient-hospital communication using smartphone platforms that were adapted to the specific pregnancy complications in the study (e.g., hypertensive disorders vs. pPROM). We also updated the instruction protocols for supervising healthcare staff in the clinical setting of home monitoring, including check lists and selection processes to identify pregnancies deemed clinically relevant for home monitoring, daily follow-up systems, electronic patient journal documentation, and the use of the most appropriate public reimbursement classifications (as none have hitherto been specifically developed for home monitoring of high-risk pregnancies).

### Participant eligibility criteria

The patients eligible for participation in the study are ≥18 years old, Norwegian-speaking, singleton pregnant women requiring intensified follow-up after at least one initial comprehensive hospital assessment. The following indications for surveillance may be relevant for home monitoring (Table 1): hypertensive disorders (chronic hypertension, gestational hypertension, and/or preeclampsia), pPROM, and previous adverse obstetric outcomes (e.g., fetal death, severe preeclampsia, preterm delivery, and/or fetal growth restriction). Exclusion criteria for home monitoring include a clinical imminent health risk to the mother and/or fetus, including (but not restricted to) non-reassuring CTG, blood pressure, infectious or clinical signs or symptoms, and/or more than 1 h travel to the hospital. Women with an expected delivery or induction of delivery within a short period will not be recruited [e.g., preeclampsia at term (≥37 weeks), prelabor rupture of membranes (PROM) ≥37 weeks, or pPROM with indication for rapid delivery (e.g., discolored amniotic fluid, suspicion of chorioamnionitis or other severe infections, or pathological CTG)]. Insufficient support at home and a lack of understanding of the relevant HOME study's technical devices (to be tested before departure from the hospital) are also exclusion criteria for being offered home monitoring.

**Table 1 T1:** Clinical definitions of the inclusion criteria for home monitoring of high-risk pregnancies.

	Inclusion criteria	Additional definitions
1	Hypertensive disorders of pregnancy	
-	✓ Chronic hypertension	✓ Hypertension (systolic blood pressure ≥140 mmHg and/or diastolic blood pressure ≥90 mmHg) identified before or during the first 20 weeks of the present pregnancy
	✓ Gestational hypertension	✓ New-onset hypertension (defined above) at ≥20 gestational weeks during the present pregnancy
	✓ Preeclampsia	✓ Gestational hypertension (defined above) in addition to new-onset proteinuria or at least one other maternal sign of organ dysfunction according to International Society for the Study of Hypertension in Pregnancy criteria from 2018 (4)
2	Preterm premature rupture of membranes	✓ Rupture of membranes at <37 gestational weeks ✓ No present uterine contractions ✓ Cephalic presentation
3	Previous adverse obstetric outcomes	✓ Intrauterine fetal death, severe preeclampsia (e.g., delivery prior to week 37 and/or severe fetal growth restriction) ✓ Preterm delivery (prior to week 37) ✓ Fetal growth restriction

### Recruitment procedure

A senior obstetrician identifies eligible pregnant women (followed up at the hospital) for home monitoring, according to the aforementioned medical inclusion and exclusion selection criteria, using a preprinted checklist. Eligible women are thereafter invited and informed by a trained research midwife, who has sufficient time with each woman to answer questions and explain the practical procedures of monitoring either in the hospital or at home. Oral and written information is provided, and written informed consent is thereafter obtained from eligible women willing to participate in the study. The timeline for participation in the study is shown in Figure 1. The midwife will, prior to study inclusion, also assess whether the woman has adequate support at home and sufficient technical understanding, including testing the patient's capability to use the specific information technology (IT) solutions necessary for home monitoring.

**Figure 1 F1:**
[figure not shown]
Flowchart of the selection of participants for home monitoring of high-risk pregnancies.

The allocation of women to the regular follow-up or home monitoring groups is based on technical equipment availability, as explained below.

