#### Hospital-monitored group details

The women in the hospital-monitored group are women who met the inclusion criteria (Table 1) and were recruited to the study from 2022 to 2024, prior to the final approvals and testing of all the technical devices for home monitoring in the clinic. In addition, some of the women eligible for home monitoring participation from 2024 will be recruited to the hospital-monitored group for reasons unrelated to the inclusion and exclusion criteria (e.g., unavailable home monitoring devices). The hospital-monitored women are treated and monitored according to standard care.

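### Group depends on device availability, and nothing described keeps recruiting staff from knowing it when they judge suitability for home monitoring, so selective entry favouring non-inferiority is possible

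*Protocol article*

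**What the plan says.** Under Recruitment procedure the allocation rule is: "The allocation of women to the regular follow-up or home monitoring groups is based on technical equipment availability, as explained below". The Method part of the abstract ties the offer itself to equipment: eligible women "are offered study inclusion to either standard care at the hospital or the home telemonitoring group, depending on available home monitoring equipment".

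Two people judge entry, both under Recruitment procedure. "A senior obstetrician identifies eligible pregnant women (followed up at the hospital) for home monitoring", using a preprinted checklist. "The midwife will, prior to study inclusion, also assess whether the woman has adequate support at home and sufficient technical understanding". According to Home-monitored group details, the research midwife also runs the device training.

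The criteria leave room for judgement. Under Participant eligibility criteria, "Exclusion criteria for home monitoring include a clinical imminent health risk to the mother and/or fetus, including (but not restricted to) non-reassuring CTG". Insufficient home support and lack of understanding of the devices are further exclusions from home monitoring.

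On timing, Study setting says: "The first woman was recruited to the hospital-monitored group in December 2022". The first home-monitored woman followed in June 2024. Hospital-monitored group details adds that, from 2024, some women eligible for home monitoring will be "recruited to the hospital-monitored group for reasons unrelated to the inclusion and exclusion criteria (e.g., unavailable home monitoring devices").

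Sample size acknowledges that allocation was not randomised and groups were not parallel, and adds 20 women for confounding. Data analysis names parity and gestational age as the adjustment variables.

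**The concern.** Device availability is a useful allocation rule only if it is unrelated to prognosis. A stock of kits may well be unrelated to prognosis. The decision that a particular woman is suitable, made by someone who knows whether a kit is free, need not be. A cautious clinician facing a borderline woman and a free kit can judge the risk too imminent or the home support too thin, and could judge the same woman suitable on a day when no kit is free.

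The women kept off home monitoring in this way would tend to be those at higher risk. That lowers the event rate in the home group for reasons unrelated to the safety of home monitoring, and in a non-inferiority comparison of severe maternal and perinatal events it pushes towards the favourable conclusion. Women recruited to hospital monitoring after June 2024 are the only controls not separated from the home group by calendar time, so the integrity of allocation in that period matters most.

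**Working it through.** **1. Can device status be known when suitability is judged?**
- Inclusion is offered to one group or the other depending on equipment (abstract, Method), so status can be known at the offer.
- The obstetrician judges eligibility specifically for home monitoring. The midwife judges support and technical ability before inclusion (Recruitment procedure).
- The imminent-risk exclusion is expressly not limited to the listed signs (Participant eligibility criteria).
- No described step withholds device status until these judgements and consent are complete.

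Before June 2024 there was no home option to steer women away from, so the mechanism applies to recruitment from then on. Selective home entry would still affect the comparison with the earlier controls.

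**2. The plan's own sample size.** Inputs from Sample size: 10% in both groups, margin 10 points, one-sided 5%, power 0.80.

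n per group = (1.645 + 0.842)² × (0.10×0.90 + 0.10×0.90) / 0.10² = 111.3, rounded up to 112, or 224 in total. Then 224 + 6 + 20 = 250. The stated figures reproduce, so this point does not concern the arithmetic of N.

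**3. Shift in the home rate (assumed inputs; the documents give none).** Let a fraction f of eligible women have risk r, with overall risk 10%. If a fraction k of that stratum is kept off home monitoring, the home rate without any treatment effect is

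h = (0.10 − f·k·r) / (1 − f·k).

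**4. Effect on the false-pass probability.** Assume home monitoring truly adds 10 points. The control rate is 10% and the home rate is 20% minus the shift. Non-inferiority is declared if the unadjusted risk difference plus 1.645 standard errors (unpooled) is below 10 points. The probability is summed over exact binomial outcomes with 112 per group.

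| f | r | k | h | Shift (points) | P(false pass) |
|---|---|---|---|---|---|
| – | – | 0 | 10.0% | 0 | 5.3% |
| 0.10 | 0.30 | 0.25 | 0.0925/0.975 = 9.49% | 0.51 | 6.5% |
| 0.10 | 0.30 | 0.50 | 0.085/0.95 = 8.95% | 1.05 | 8.1% |
| 0.20 | 0.25 | 0.25 | 0.0875/0.95 = 9.21% | 0.79 | 7.3% |
| 0.20 | 0.25 | 0.50 | 0.075/0.90 = 8.33% | 1.67 | 10.4% |

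**5. Does the plan's response remove it?** Extra women reduce variance, not bias. By normal approximation, a fixed 1-point shift gives 7.6% with 112 per group and 7.8% with 125. Parity and gestational age measure neither the indication nor its severity, so adjusting for them does not restore balance on what the clinicians are judging.

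**The case against.** The strongest reply is that this is a possibility, not an error. No text says who looks up device stock or when, and the selection flowchart (Figure 1) is not available to check. Recruitment procedure already places the checklist, information on both kinds of monitoring, consent and the suitability assessment ahead of its sentence on allocation. Hospital-monitored group details says later controls are eligible for home monitoring and enter the hospital group for reasons unrelated to the criteria. Enrolling as a control a woman who would have been excluded had a kit been free would breach that statement. The study is openly observational and states that women were not randomised. Most controls predate June 2024, and no concurrent-only analysis is described.

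Much of this stands. A reader might infer that women are being steered, that the order of steps is wrong throughout, or that the absence of randomisation is itself the fault. The documents support none of these: they show no instance of steering, the written order is roughly right, and the design is disclosed. Nor do the assumed scenarios support a shift of 2 points or a false-pass chance of 12%; they stop at 1.67 points and 10.4%. The table counts only the home side, because the text intends concurrent controls to be eligible women.

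What remains is that the statement on unrelated reasons is an intention without a described procedure. It also governs women already judged eligible, whereas selection would act at that judgement. The checklist fixes the questions but leaves the answers to discretion. The order of steps in the text does not stop staff from knowing device status beforehand, and the abstract's wording suggests that they may.

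**Conclusion.** The point holds in a limited form. From June 2024 the group depends on equipment availability, and nothing described separates that knowledge from discretionary judgements related to prognosis. Selective entry to home monitoring is possible, would tend to favour non-inferiority, and is not removed by the planned adjustment.

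Its size cannot be derived from the documents. The illustrated rise in the false-pass chance, from 5.3% to between 6.5% and 10.4%, rests on the assumed strata and steering fractions, an unchanged 10% control rate, 112 women per group and an unadjusted risk difference. It shows that modest selection could matter; it is not an estimate of bias in this study. A change is worth making for the remaining recruitment, but the point does not by itself invalidate the comparison.

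**What to change.** For remaining recruitment, state under Recruitment procedure that the signed checklist, the assessment of home support and technical ability, and consent to either group are completed and time-stamped before equipment availability is looked up, for example in a log opened only after consent. Then assign home monitoring whenever the equipment needed for that woman's indication is free, in order of consent. The wording must refer to indication, because the devices differ between the hypertensive and pPROM groups.

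Record availability at each consent. Report eligibility decisions, indication and gestational age according to whether equipment was free. This makes the assumption that availability is unrelated to case mix open to checking.

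The cost is a firmer order of steps already described and a simple log. It needs no extra patients or visits, and N is unchanged. The downside is that some suitability assessments will be done for women who then receive no equipment. Women already recruited, including the controls from before the home option opened, are not covered, so confounding with calendar time remains and has to be handled separately.

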#### Hospital-monitored group details

The women in the hospital-monitored group are women who met the inclusion criteria (Table 1) and were recruited to the study from 2022 to 2024, prior to the final approvals and testing of all the technical devices for home monitoring in the clinic. In addition, some of the women eligible for home monitoring participation from 2024 will be recruited to the hospital-monitored group for reasons unrelated to the inclusion and exclusion criteria (e.g., unavailable home monitoring devices). The hospital-monitored women are treated and monitored according to standard care.

